## Methods

### Study design

This prospective trial will be a single-center, open-label, randomized, controlled, superiority clinical trial. A total of 2594 patients with AMI (both acute ST-segment elevation and non-ST-segment elevation myocardial infarction) will be recruited and randomized in a 1:1 fashion to one of the two treatment arms from October 2020 through October 2025. The protocol was designed according to the Standard Protocol Items: Recommendations for Interventional Trials (SPIRIT) 2013 Statement [12]. The protocol was designed in accordance with the SPIRIT 2013 Statement (Standard Protocol Items: Recommendations for Interventional Trials). The SPIRIT Checklist for this protocol is detailed in the Supplementary Material, Additional file 2.

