### Inclusion criteria

Patients eligible for enrollment will be men and women, 18 years of age or older, who are diagnosed with AMI. Diagnostic criteria for AMI were determined according to the Fourth Universal Definition of Myocardial Infarction [14].

A patient with elevated cardiac biomarkers (mainly cTnT) above the 99th percentile of the upper limit of the reference value and who meets at least one of the following conditions is considered to be diagnosed with AMI.Ischemic symptoms.Electrocardiograph has typical manifestations.Echocardiography showed segmental abnormal ventricular wall motion.Intravascular thrombosis confirmed by coronary angiography or autopsy.

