### Blinding

This is an open-label trial. Trial participants, investigators, caregivers, outcome assessors, and data analysts are not blinded to the group assignment.

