#### Secondary outcome

Secondary outcomes will be clinical complications and laboratory results serve as surrogate end-points for prognosis. The secondary outcomes include the following:The incidence of MACE (including heart failure, malignant arrhythmias, cardiogenic shock, cardiogenic death, and recurrent myocardial infarction) during hospitalization or at 30-day follow-upThe incidence of myocardial infarction-related mechanical complications during hospitalization or at 30-day follow-upThe difference between the trial groups in left ventricular ejection (LVEF) measured by echocardiography at baseline, 7th day, and 30th day

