### Definition

In this study, MACE is defined as heart failure, malignant arrhythmias, cardiogenic shock, cardiac death, and recurrent myocardial infarction.According to the AHA/ACC/HFSA Guidelines for Managing Heart Failure [15], the diagnosis of heart failure is mainly based on clinical manifestations and physical examination: (1) typical clinical manifestations of new-onset heart failure (such as dyspnea, ankle edema, fatigue), (2) moist rales could be heard in more than one-third of the lung fields, (3) chest X-ray showed non-cardiac pulmonary edema or pulmonary obstruction, and (4) abnormal levels of brain natriuretic peptide or B-type natriuretic peptide precursor.Malignant arrhythmias are defined as atrial fibrillation/flutter, ventricular tachycardia, and high-degreee atrioventricular block.The criteria for cardiogenic shock include less than 90 mmHg systolic blood pressure, continuing for at least 30 min, clinical signs of pulmonary congestion, and organ perfusion for signs of damage to at least one of the following performance: the mental state changes, skin and limbs cold and wet, oliguria, and urinate less than 30 ml per hour.Cardiac death is defined as death from any of several cardiac causes.Recurring myocardial infarction is defined as another myocardial infarction 28 days after the onset of acute myocardial infarction, with ST-elevation ≥ 1 mm recurs, or new pathogomonic Q waves appear in at least two contiguous leads, especially when accompanied by symptoms of ischemia.Myocardial infarction-related mechanical complications include cardiac rupture, ventricular septal rupture, and papillary muscle rupture.

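### Recurrent infarction needs recurrent ST-elevation or new Q waves, so a trial that enrols NSTEMI cannot count reinfarctions with neither sign

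*Protocol article*

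**What the plan says.** The protocol article uses one rule for infarction at entry and another for infarction as an outcome.

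- **Entry (Inclusion criteria).** The cited standard is the Fourth Universal Definition: "Diagnostic criteria for AMI were determined according to the Fourth Universal Definition of Myocardial Infarction". The operative rule starts from "A patient with elevated cardiac biomarkers (mainly cTnT) above the 99th percentile of the upper limit of the reference value" and adds at least one of ischaemic symptoms, typical ECG, segmental wall-motion abnormality or confirmed thrombus. ST-elevation and Q waves are not required.
- **Population (Study design).** The trial takes "both acute ST-segment elevation and non-ST-segment elevation myocardial infarction".
- **Outcome (Definition).** "Recurring myocardial infarction is defined as another myocardial infarction 28 days after the onset of acute myocardial infarction", and it must come "with ST-elevation ≥ 1 mm recurs, or new pathogomonic Q waves appear in at least two contiguous leads". Symptoms are supportive only: "especially when accompanied by symptoms of ischemia". No troponin or other biomarker appears.
- **Where it is used (Secondary outcome).** It is one part of MACE, "including heart failure, malignant arrhythmias, cardiogenic shock, cardiogenic death, and recurrent myocardial infarction". It is not listed as an outcome on its own.
- **Who judges it (Blinding).** "Trial participants, investigators, caregivers, outcome assessors, and data analysts are not blinded to the group assignment".

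Table 1, under Follow-up, schedules ECG, myocardial enzymes and echocardiography at baseline and on days 7, 10 and 30.

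**The concern.** The outcome rule makes one of two ECG signs a condition. A patient with recurrent chest pain, a second troponin rise and ST depression satisfies the entry rule again but can never satisfy the outcome rule. An NSTEMI patient whose second event resembles the first is not countable. This is a stated rule that gives the wrong count, not a detail that an article would leave to the full protocol or analysis plan.

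There is a second, weaker problem. The rule does not say which earlier tracing a Q wave must be new against, does not exclude the index territory, and asks for no new biomarker rise. A Q wave that belongs to the first infarct might therefore be recorded as a second.

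Missed events reduce the information in the component. False events, if equally likely in both arms, pull its risk ratio toward 1. Because assessors know the allocation, a criterion that turns on whether an ECG change is new also leaves room for judgement to differ by arm.

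**Working it through.** **No figure to reproduce.** The article gives no rate for recurrent infarction, for reinfarction without ST-elevation or Q waves, or for late Q-wave evolution. Its only design figure concerns mortality and reproduces: hazard ratio ln(1 − 0.0534)/ln(1 − 0.089) = 0.589; Freedman's method gives 157 events; 157/(0.089 + 0.0534) = 1102.5 per arm, against 1102 stated; 1102/0.85 ≈ 1297. None of this depends on the reinfarction rule.

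**The two rules applied to the same patients**

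| Second event | Entry rule | Outcome rule |
|---|---|---|
| Troponin raised, symptoms, ST-elevation recurs | Infarction | Counted |
| Troponin raised, symptoms, ST depression, no Q waves | Infarction | Not counted |
| Troponin raised, new wall-motion loss, no ST-elevation or Q waves | Infarction | Not counted |
| Q wave of the index infarct first seen on a later ECG, no new event | Not a separate infarction | Unclear: no comparison ECG or new biomarker rise is stated |

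All rows are subject to the 28-day wording. Rows two and three follow from the text without any assumption. Importing the entry rule through the phrase about another infarction does not rescue them, because the ECG condition still applies on top.

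Row four depends on timing. If the 28-day phrase means within 28 days, a Q wave first seen on the day 7 or day 10 ECG could be set against baseline. If it means from day 28 onward, most index Q waves will already have appeared, but a day 30 tracing compared only with baseline could still show one as new.

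**Illustration of size within MACE (all inputs assumed, except that the overlap is set near the 40.2 to 40.5% in-hospital heart failure quoted in Background).** Let true reinfarction be 2 to 4%, let 40% of those patients already be counted through another component, and let 30 to 60% of reinfarctions lack both ECG signs. The MACE rate then falls by:

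- reinfarction 4%: 4 × 0.60 × 0.30 = 0.72 to 4 × 0.60 × 0.60 = 1.44 percentage points;
- reinfarction 2%: 0.36 to 0.72 percentage points.

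For false events, suppose true MACE is 45% against 36% (risk ratio 0.80):

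- 2% of event-free patients miscounted: 45 + 0.02 × 55 = 46.1; 36 + 0.02 × 64 = 37.28; ratio 0.81;
- 5% miscounted: 45 + 0.05 × 55 = 47.75; 36 + 0.05 × 64 = 39.2; ratio 0.82.

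**The component alone (assumed risk ratio 0.60, 1102 per arm, two-sided 0.05).**

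| Control risk | All counted | 70% counted | 40% counted |
|---|---|---|---|
| 4% | 57% power | 43% | 27% |
| 2% | 32% power | 24% | 15% |

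With 4% risk and 70% counted, adding 2% or 5% false events moves the observed risk ratio to 0.77 or 0.86. These component figures show direction only, since reinfarction is not analysed as a listed outcome of its own.

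**The case against.** The best defence is that the ECG terms qualify an infarction that must first be present. A reader might infer that an ECG change alone makes an event, so that pericarditis, an aneurysm or ordinary evolution of the index infarct counts with no new necrosis. The text does not say that. It asks for another infarction and for new Q waves, and a condition that is not an infarction, or is the same infarction, is outside those words. This stands, and it reduces the false-event half to a possibility. It does not remove it. The entry rule asks only for a troponin level above the threshold, not a new rise, and troponin may still be raised from the index event.

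It is also fair that the entry rule is a poor model for a second event. Soon after an infarct, residual troponin plus an existing wall-motion abnormality could satisfy it. A different reinfarction rule is therefore not wrong in itself. The defect is that the rule chosen cannot see one form of the disease the trial enrols.

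Finally, the component sits inside a secondary composite probably dominated by heart failure, so the practical effect is small. That stands too.

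**Conclusion.** The point holds for missed events and, more weakly, for false ones. Reinfarctions with neither ST-elevation nor new Q waves are never counted as recurrent infarction; such a patient enters MACE only if another component occurs. Q waves of the index infarct might be counted, to an extent that cannot be judged until the 28-day wording is settled.

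The size cannot be derived from the documents. A reader might infer that 30 to 60% of reinfarctions go uncounted, or that 5% of 1297, about 65 patients per arm, would be falsely recorded and could outnumber the true events. Neither percentage has a source in the article, and it gives no reinfarction rate for comparison. Under the assumptions shown above, the effect on MACE is about 0.4 to 1.4 percentage points from missed events and a shift in risk ratio from 0.80 to at most about 0.82 from false ones. That is modest. Nor can one assume that false events are unrelated to treatment, because assessment is unblinded. The mortality primary outcome and its sample size are unaffected. The wording should be changed, but it does not threaten the trial's main conclusion.

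**What to change.** Rewrite the outcome definition in the same edit that settles the 28-day wording:

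1. Recurrent infarction, for outcome counting, is a new troponin rise from a stable or falling level plus at least one of: ischaemic symptoms; new ischaemic ECG change, including but not limited to ST-elevation or Q waves; new wall-motion abnormality; or thrombus. This goes beyond the entry rule, which asks for no new rise.
2. Q-wave evolution in the index territory alone does not count, and the ECG used for comparison is named.
3. Where no troponin sample exists, the present ECG rule applies, with symptoms required.

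**Cost.** The change is to endpoint wording and draws largely on tests already in Table 1, though the table says myocardial enzymes without naming troponin. It needs ethics and regulatory approval under Auditing and amendment. Recruitment began in October 2020, so events already recorded must be re-reviewed against the new wording, preferably with allocation removed from the records. Events after discharge are sought at a day 30 telephone or face-to-face contact, so some readmissions may lack troponin data and will fall to the third rule.

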### Follow-up

During the informed consent period, the researcher will have the patient consider whether they can complete the follow-up and then decide whether to participate in the study. In order to facilitate participant retention and complete follow-up, addresses and phone numbers of participants and their families will be collected after consent was obtained. In addition, we will request the physician in charge who is trusted by the patient to assist in the follow-up of the patient. The follow-up period will be divided into two phases, during hospitalization and after discharge. According to statistics, the average hospitalization time of patients with AMI in the First Affiliated Hospital of Shantou University Medical College was 10 days. During hospitalization, the staff will be scheduled to follow up daily, mainly to understand the occurrence of adverse events and the compliance of patients with medication, for a maximum of 30 days. Patients who have been hospitalized for less than 30 days will be followed up by phone or face-to-face on day 30, mainly to check the patient’s survival status and any readmission within 30 days. If there is a readmission within 30 days, further information on the reason for the admission and the presence of adverse cardiovascular events will be obtained. The detailed study schedule is listed in Table 1. Patients who completed the 30-day follow-up were considered to have met the clinical and trial requirements. Patients who discontinued the study drug prematurely will be marked as off-study drug/on study and will follow the same schedule of events as those patients who continue study treatment.

**Table 1 Tab1:** Timeline of trial procedures and follow-up schedule

Study period															
	Screening	Baseline	Follow-up												
Time point (days)	− 1	0	1	2	3	4	5	6	7	8	9	10	etc	30th	Close-out
Eligibility check	X	X													
Informed consent	X														
Relevant medical history taken	X	X													
Physical examination	X	X	X	X	X	X	X	X	X	X	X	X	X	X	
Full blood count		X							X			X		X	
Lipid levels		X							X			X		X	
Liver and renal function		X							X			X		X	
Myocardial enzymes		X							X			X		X	
C-reactive protein		X							X			X		X	
Pro-BNP		X							X			X		X	
HBALC		X							X			X		X	
Electrocardiogram		X							X			X		X	
Echocardiography		X							X			X		X	
All-cause death		X	X	X	X	X	X	X	X	X	X	X	X	X	X
MACE		X	X	X	X	X	X	X	X	X	X	X	X	X	X
Serious adverse events		X	X	X	X	X	X	X	X	X	X	X	X	X	X

*Pro-BNP* N-terminal pro-brain natriuretic peptide, *MACE* major adverse cardiovascular events

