### Outcome measurements

Hospitalized patients will be followed daily until the occurrence of a primary end-point event or discharge from the hospital. Telephone follow-up will be conducted on the 30th day after admission to understand the survival status of the patients. For patients who have been hospitalized for more than 30 days, end-point events will be collected on day 30 of hospitalization.

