### Data collection and management

At enrollment, we will collect demographic information of participants, including age, height, weight, blood pressure, heart rate, past medical history, smoking history, and laboratory parameters (including leukocytes, neutrophils, creatinine, uric acid, myocardial enzymes, lipid profile, pro-BNP, CRP, LEVF, LVd, LVS) at admission. Besides, death, heart failure, malignant arrhythmias, cardiogenic shock, recurrent myocardial infarction, and other conditions of patients will be recorded during the hospitalization or follow-up at the 30th day. Case report forms (CRFs) will be used to record all participant data. This task will be completed by the researchers, who will also enter the data into an electronic database by duplicate entry using the EpiData software (Denmark, version 3.1). All data will be stored in the scientific research platform of the First Affiliated Hospital of Shantou University Medical College, which is a secure server with limited access and supported for anonymity analysis and review.

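### The Follow-up text asks about cardiovascular events after discharge only where there was a readmission, while the outcome definition, Table 1 and the data collection section have MACE recorded to day 30 in everyone

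*Protocol article*

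**What the plan says.** Three places in the protocol article treat MACE as known at day 30 for every patient.

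- Secondary outcome: MACE incidence is defined as "including heart failure, malignant arrhythmias, cardiogenic shock, cardiogenic death, and recurrent myocardial infarction) during hospitalization or at 30-day" follow-up.
- Data collection and management: the MACE components "will be recorded during the hospitalization or follow-up at the 30th day". No readmission condition is attached.
- Table 1: the MACE row is marked from baseline through each listed day, at day 30 and at close-out. Physical examination, electrocardiogram, echocardiography and pro-BNP are also marked at day 30.

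Two places describe how patients are actually contacted, and they are narrower.

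- Follow-up: "During hospitalization, the staff will be scheduled to follow up daily, mainly to understand the occurrence of adverse events" and drug compliance. Patients discharged before day 30 are "followed up by phone or face-to-face on day 30, mainly to check the patient’s survival status and any readmission within 30 days". Then: "If there is a readmission within 30 days, further information on the reason for the admission and the presence of adverse cardiovascular events will be" collected.
- Outcome measurements: "Telephone follow-up will be conducted on the 30th day after admission to understand the survival status of the patients".

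The Follow-up section gives an average stay of 10 days. The Blinding section states that participants, investigators, caregivers, outcome assessors and analysts all know the allocation.

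**The concern.** The two descriptions of the day-30 contact contain no MACE enquiry for a patient who went home and was not readmitted. Heart failure or atrial fibrillation treated in a clinic could then be counted as no event, while the same condition on the ward would be found by daily follow-up. The composite would join close surveillance before discharge to a much weaker check after it.

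The join falls at discharge, which comes after randomisation. If the arms differ in length of stay, they also differ in days under close surveillance, and detected MACE can differ with no true effect. The article itself lists diarrhoea, constipation and bacteraemia as possible reactions and suggests a laxative effect, so an effect on stay is conceivable, although it gives no data on this. Even with equal stays, non-fatal events to day 30 would be under-counted.

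**Working it through.** **The passages side by side.** The outcome definition, the data collection section and Table 1 say what is to be recorded. The Follow-up and Outcome measurements sections say by what contact. For a patient discharged on day 10, no contact is described until day 30, so the Table 1 MACE marks in between can be met only by asking back at day 30. The text ties that question to readmission. The contact may also be by telephone, and a call cannot itself supply the lung findings, chest X-ray and natriuretic peptide that the Definition section uses for heart failure.

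**The plan's own figure.** No figure is given for MACE. The sample size for mortality reproduces:

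- Hazard ratio = ln(1 − 0.0534) / ln(1 − 0.089) = 0.589.
- Freedman's method (two-sided 0.05, 90% power) gives 157 events.
- Mean event rate = (0.089 + 0.0534) / 2 = 0.0712; 157 / 0.0712 / 2 ≈ 1102 per arm.
- With 15% dropout: 1102 / 0.85 = 1296.5, rounded up to 1297 per arm.

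Nothing in this point changes that number.

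**Share of the window after discharge.** (30 − 10) / 30 = 67% of days. This is not 67% of risk, because risk need not be even over the 30 days.

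**Patients who could be missed (illustration).** The Background gives in-hospital heart failure of 40.2–40.5%. Those patients are already MACE cases and cannot be missed in an incidence count, which leaves about 60%: 0.60 × 1297 ≈ 778 per arm. Assume that 3–6% of them have a first non-fatal event after discharge and that none is readmitted:

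- 0.03 × 778 ≈ 23
- 0.06 × 778 ≈ 47

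Other in-hospital MACE would lower these counts, as would any readmission.

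**Spurious difference if stay differs (illustration, all inputs assumed).** In-hospital MACE is 40%. A further share q of all patients has a first non-fatal event spread evenly over days 10–30. A fraction r of those events leads to readmission and only those are detected. One arm stays d days longer. There is no true effect.

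- Detected, shorter stay: 0.40 + r·q
- Detected, longer stay: 0.40 + d·q/20 + r·(q − d·q/20)
- Difference: (1 − r)·d·q/20

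| q | r | d (days) | Difference (percentage points) | Chance of a significant result in that direction |
|---|---|---|---|---|
| 0.05 | 0.7 | 1 | 0.08 | 2.7% |
| 0.10 | 0.5 | 2 | 0.50 | 4.4% |
| 0.15 | 0.3 | 3 | 1.58 | 12.4% |

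The last column uses 1297 per arm and a two-sided 0.05 test, for which the chance in one direction should be 2.5%. The first and last rows are the extremes of the grid examined (q 5–15%, r 30–70%, d 1–3 days). The effect is small unless stay differs by several days and most post-discharge events go undetected.

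**The case against.** The strongest reply is that the article never says other events go unasked. The contact is described as "mainly to check the patient’s survival status and any readmission within 30 days", and the word mainly leaves room for more. The data collection section and Table 1 carry no readmission condition. Table 1 schedules examination, electrocardiogram, echocardiography and pro-BNP at day 30, the LVEF outcome needs a day-30 measurement, and a face-to-face contact is allowed. On that schedule, ongoing heart failure or atrial fibrillation could be found without a readmission. This stands: a reader might infer that events are sought only in readmitted patients, but that is one reading of one paragraph. What the article shows is a conflict over what happens at day 30.

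Three further limits also stand.

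- Cardiac death can be found in everyone, because survival is tracked by telephone and electronic records and the cause of death is recorded. Shock and reinfarction would ordinarily lead to admission. The gap is therefore mainly heart failure and arrhythmia managed outside hospital.
- A reader might infer that unblinded staff control length of stay. The article does not say who decides discharge or on what criteria, and it gives no reason to expect that stay will differ by arm.
- Applying 3–6% to all 1297 patients would give 39–78 per arm, but that counts patients who already had an in-hospital event.

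It could also be said that day-30 question wording belongs in the full protocol or the case report form. That covers the wording, but not a condition that the article states and its own table contradicts.

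**Conclusion.** The point holds as an inconsistency with a consequence. The Follow-up and Outcome measurements sections describe a day-30 contact that does not secure what the Secondary outcome section, Table 1 and the data collection section require. If the narrower text is followed, non-fatal MACE without readmission can be missed over about 20 of 30 days for an average stay, and detection depends on length of stay in a fully unblinded trial.

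The size is uncertain. The figure of about 23–47 missed patients per arm rests on an assumed 3–6% rate and on no readmissions, which is a worst case. The spurious difference of 0.1 to 1.6 percentage points rests on the assumed rates and on stays that differ by 1–3 days. It would be wrong to conclude that any difference in stay must bias MACE, or that bias is present: with equal stays, the same under-counting would be expected in both arms. The outcome is secondary. The point should be corrected, and it does not threaten the primary comparison.

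**What to change.** Rewrite the Follow-up and Outcome measurements sections to agree with Table 1 and the data collection section. At the day-30 contact already planned, ask every surviving patient in both arms the same questions on the non-fatal MACE components, whether or not there was a readmission, and obtain records for any positive answer. Replace the single outcome that joins the two periods with two separately labelled outcomes: in-hospital MACE, and MACE to day 30.

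The cost is a slightly longer call, some changes to the case report form, and some patient-reported events that need confirmation from records. A common day-30 enquiry reduces the dependence on length of stay but does not remove it, since recall at day 30 is still weaker than daily follow-up; labelling the two outcomes separately lets readers see this. The article states that recruitment was under way, and answers not collected at day 30 are hard to recover later, so the change is worth making early. The primary outcome and the sample size stay as they are.
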